### Concealment mechanism {16b}

Participants will be randomized using random number generator. The allocation concealment mechanism will be used once the participants will not be informed of the allocation group prior to the intervention, which takes place after all baseline measurements have been completed.

### Implementation {16c}

An independent researcher will generate the allocation sequence. The research team will then enroll participants and assign them to interventions. The participants will be informed about the group they were assigned (i.e., based on a random number generator performed autonomously by an independent researcher) by email.

## Assignment of interventions: blinding

### Who will be blinded {17a}

Baseline assessment will take place prior to randomization; thus, at this point, participants and field work staff will be unaware of group allocation. After baseline, due to the nature of the intervention, it will not be possible to blind participants or staff.

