### Procedure for unblinding if needed {17b}

After randomization is performed and when communicating to the participants their group allocation, unblinding will be required. At this time, the trial manager, data coordinator, implementation support facilitators, care home managers, and participants will have access to group allocations.

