##### Body composition and postural inequality assessment

Participants will be weighed to the nearest 0.01 kg while wearing minimal clothes and without shoes, on an electronic scale (TANITA BC-601 scale). Height will be measured to the nearest 0.1 cm with a stadiometer (Seca, Hamburg, Germany). BMI will be calculated as body mass (kg)/height^2^ (m). BMI will be further categorized into normal weight (<25 kg/m^2^), overweight (25–29.9 kg/m^2^), and obesity (>30 kg/m^2^). Waist circumference will be measured with the participants in a standing position, over the naked skin, to the nearest 0.1 cm. The tape is applied horizontally just above the uppermost lateral border of the right ilium at the end of a normal expiration. The mean of two measurements will be considered. If the two measurements differ by more than 1 cm, a third measurement will be performed, and the two closest measurements will be averaged.

Further, body composition will be assessed using bioimpedance (BIA) (101 Anniversary, Akern, Florence, Italy). BIA has been widely used in the sports field for the assessment of body composition and cellular health. BIA is not subject to errors related to prediction equations since it interprets the raw bioimpedance values [resistance (R) and reactance (c)], and it is an easy way to use and non-invasive method. BIA will be performed by a phase-sensitive single-frequency bioimpedance analyzer. Vector length (VL) and phase angle (PhA) will be calculated. This former parameter is an indicator of cellular health. Also, body fat-free mass will be estimated with BIA, while using previous validated equations. Body fat mass will be calculated by subtracting fat-free mass from total body mass. The participants will be fasting for at least 8 h, with a good night sleep, and all metallic accessories will be removed. The participants will be lying down for 5 min prior to this assessment.

Finally, two pictures of the participants will be taken (frontal and lateral), so that postural unbalances can be detected in all assessment moments. This is a simple and quick procedure to assess postural alterations.

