
#### Procedures

After complying with the inclusion criteria, participants will be contacted via email to schedule their baseline evaluation, as well as be informed in advance about the conditions of the study, and that they must attend to the evaluation morning fasting and with an empty bladder. The day before the evaluation, participants will receive an email confirming the place, date, and time of their procedure, and a reminder of all the criteria they must fulfil to be assessed.

On the scheduled day, each participant will sign the free and informed consent and will be identified through an alphanumeric code (e.g., suf01), to maintain the anonymity of their information. Initially, it will be confirmed with each participant whether they remain fasting and if they have an empty bladder (as agreed in advance), and the information will be registered in a Microsoft Excel software file®. The start of the evaluation will be by the measurement of body mass (TANITA BC-601 scale), height (Seca, Hamburg, Germany), and waist circumference (according to the World Health Organization: the midpoint between the lower border of the rib cage and the iliac crest, after a normal expiration) [71]. The height measurement will be performed with the feet slightly apart, with nearby heels, a neutral spine position, and the head according to the Frankfurt plan.

After the measurement’s procedures, we will ask participants to remove all their metal belongings to evaluate their body composition, using BIA. They must lie in the supine position for about 5 min, with their legs slightly apart and arms along the body for placement of the electrodes in the standardized points (right hand and foot) [71], thus enabling the verification of reactance and resistance values. The postural evaluation will take place then, through two photos of the evaluated standing, and in two different positions (front and side), with the feet slightly apart at the width of the hip, relaxed shoulders, and spine in a neutral position. After an explanation of how to use the ActivPAL, the participants will receive the ActivPal device, which will be placed, with the aid of a waterproof pharmacological dressing, at the right thigh's midpoint.

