### Data management {19}

Data entry, processing, and management will be done by two researchers supervised by the PI as follows steps:We will create a database with all measures obtained in data collection. An identification code will be generated for each participant to guarantee their privacy.A data set will be exported and saved by Qualtrics software containing all information obtained via questionnaires.We will also extract and save raw files based on ActivPAL information as well as a database will be created with PA, SB, and sleep information.A New database will collate and store anonymized data securely with all domains of the project.Data quality control will be accomplished by documentation checks, monitoring putative punching errors, and systematic controls.

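### The reason given for not blinding staff after baseline does not extend to processing coded ActivPAL files, rating stored posture photos or running the analysis, and the data coordinator's access to allocation is not justified

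*Protocol article*

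**What the plan says.** Who will be blinded {17a} first says that at baseline "participants and field work staff will be unaware of group allocation", because randomization comes later. It then says: "After baseline, due to the nature of the intervention, it will not be possible to blind participants or staff". No role is excepted.

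Procedure for unblinding if needed {17b} adds that, once participants are told their group, "the trial manager, data coordinator, implementation support facilitators, care home managers, and participants will have access to group allocations". No reason is attached to any role. Care home managers do not fit a trial of university office workers, so the list needs rewriting in any case.

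Other sections describe work done away from the desk:

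- Sedentary and PA pattern assessment: ActivPAL data are classified by a named algorithm.
- Body composition and postural inequality assessment: "two pictures of the participants will be taken (frontal and lateral), so that postural unbalances can be detected in all assessment moments".
- Procedures: each participant "will be identified through an alphanumeric code (e.g., suf01), to maintain the anonymity of their information".
- Data management {19}: "An identification code will be generated for each participant to guarantee their privacy", and "Data entry, processing, and management will be done by two researchers supervised by the PI".
- Sequence generation {16a} and Implementation {16c}: the allocation is generated by a researcher who has no part in recruitment or data collection.

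**The concern.** A sit-stand desk cannot be hidden from the person who uses it or from the person who installs it. The protocol uses this fact to answer the blinding question for staff in general. Staff who only handle coded files, stored pictures or a data set are not exposed to the desk by the nature of the intervention. They know the arm only if someone tells them, and {17b} provides for telling at least one data role.

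Three steps are at stake:

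- **Photo rating.** Postural inequality is read from two pictures, and the article states no scoring rule. A rater who knows the arm and the time point has room to favour the desk group.
- **Analysis.** Statistical methods {20a} allows non-parametric tests if exploratory analysis shows non-normality, and the list of primary outcomes in Outcomes {12} is open-ended. An analyst who can see the arms makes such choices knowing which result each would give.
- **Device processing.** The exposure here is smaller, because an algorithm does the classification.

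The self-reported outcomes cannot be masked in this design. That is a reason to protect the steps that can be.

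**Working it through.** The protocol gives no figure on this point and none is needed to test it. The check sets the stated reason against each task.

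| Task | Where described | Contact with desk or participant? | Does the stated reason apply? |
|---|---|---|---|
| Using the desk, answering questionnaires | Intervention description {11a}; Psychosocial assessments | Yes | Yes |
| Assembling desks, giving guidance | Intervention description {11a} | Yes | Yes |
| On-site measurement after baseline | Procedures | Yes, meets the participant | Yes, in practice |
| Processing ActivPAL files | Sedentary and PA pattern assessment; Data management {19} | No | No |
| Rating stored posture photos | Body composition and postural inequality assessment | No, only the image | No |
| Running the analysis | Statistical methods {20a} | No | No |

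**Are these steps masked elsewhere?** No section of the article assigns a masked processor, rater or analyst.

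**Are the means at hand?**

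1. The example code, suf01, carries no arm information, and Confidentiality {27} says the database holds no identifying elements.
2. The codes were introduced for privacy. They mask only if the person doing the task has no access to the list that links code to arm.
3. An independent researcher already generates the sequence and could hold that list.
4. The data coordinator's access under {17b} works against point 2 if that role takes part in processing, rating or analysis. The article does not say whether it does.

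**Is it still useful?** Trial status says the intervention began on 1 March 2023 and that two assessments are still to come. The month-6 and month-9 files and photos can therefore still be handled masked, by people who do not yet know the arms.

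**Size.** The documents contain nothing from which a rating or analyst bias could be computed.

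**The case against.** The strongest reply is that {17a} speaks of field work staff in one sentence and of staff in the next. Read in sequence, the second sentence concerns people who meet participants, and for them it is correct. A reader might infer that the protocol rules out blinding of all staff, but the text does not say *all*. This stands, and it limits the point to a statement that is too broad or unclear. Even on the narrow reading no section masks anyone else, and the data coordinator still receives the allocation.

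A reader might also infer that the two data researchers, the photo rater and the analyst are unmasked by rule. The list in {17b} does not name them, and nothing says that the data coordinator is one of them. Detailed rater and analyst procedures may also sit in a fuller document. What the article itself fixes is the general reason and the one data role on the list.

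A third tempting step is to claim bias in the primary outcome. The article describes algorithmic classification that covers non-wear, sitting, standing and stepping, and it states no manual step. The claim is not supported beyond a small possible effect.

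Finally, one could attach a false-positive rate. With 34/2 = 17 per arm and no true effect, assumed shifts of 0.16, 0.32 and 0.40 SD in a two-sample t-test at 5% give rejection rates of about 7%, 15% and 21%. These should not be used as estimates for this trial. The shifts are assumptions without a source in the documents. The planned analysis is a repeated measures ANOVA over three time points, and allocation is by site.

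Practical objections also hold. The trial is running and the team meets weekly on participants, progress and outcome data. Nudges and video clips show participants at their desks. Raters may recognise colleagues in the photos. Because the control group gets desks after month 6, standing patterns may also suggest the arm.

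**Conclusion.** The point holds in a limited form. The stated reason covers participants and staff who deliver the intervention or meet participants. It does not cover file processing, photo rating or analysis. The article masks none of these and gives the data coordinator the allocation without a stated need.

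The exposure falls mainly on one secondary outcome, posture from photos, and on analyst choices. For the ActivPAL outcomes it is probably small. No size can be given from the documents.

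The conclusion rests on two assumptions: that some team members do not yet know the arms, and that photo rating involves some judgement, since no scoring rule is stated. It is a cheap improvement and does not call the design into question.

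**What to change.** 1. In {17a}, limit the statement that blinding is impossible to participants and to staff who deliver the intervention or meet participants.
2. For the remaining assessments, have existing team members who do not know the arms process the ActivPAL files and rate the photos. They should work by code, in random order and with the time point hidden.
3. Give the analyst arms labelled A and B until the primary model is final. The independent researcher who generated the sequence holds the key.
4. In {17b}, remove the data coordinator from the list. If that role already knows the allocation, state that it takes no part in processing, rating or analysis. Correct the care home entry at the same time.

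**Cost.** No new post should be needed, but there is some added work in recoding the arms and randomizing the order of photos. The people chosen must stay out of desk installation and out of those parts of the weekly meetings that reveal allocation. Masking will remain imperfect because participants are colleagues and standing patterns may suggest the arm, and the report should say so.

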### Procedure for unblinding if needed {17b}

After randomization is performed and when communicating to the participants their group allocation, unblinding will be required. At this time, the trial manager, data coordinator, implementation support facilitators, care home managers, and participants will have access to group allocations.

## Data collection and management

### Plans for assessment and collection of outcomes {18a}

#### Primary data collection

##### Sedentary and PA pattern assessment

We will collect sedentary and PA pattern data derived from an ActivPAL inclinometer/accelerometer monitor (model ActivPAL4; PAL Technologies Ltd., Glasgow, UK), while using the CREA (v1.3) classification algorithm that allows to distinguish non-wear, lying/sitting, standing, cycling, seated during transport, and stepping time as well as the number of steps and stepping cadence. The ActivPAL combines the information from an inbuilt inclinometer and accelerometer and is the reference objective method for monitoring sedentary activity and transitions from and to this behavior among researchers. Due to its position on the thigh, the ActivPAL permits the distinction between standing (vertical position) from sitting or lying (horizontal position), and the accelerometer data allows to distinguish stationary upright activities (i.e., standing) from upright activities with movement (i.e., stepping). The following variables will be calculated from the device:Mean minutes spent sitting,Mean minutes spent standingMean minutes spent steppingMean number of sit-to-upright transitionsMean minutes spent in prolonged (e.g., bouts of ≥30 min) sittingMean minutes spent sleeping

These variables will be calculated across the total waking day. Participants will wear the device on their right thigh 24 h/day for 7 days at baseline, repeating this assessment at the end of the intervention (after 6 months), and after the follow-up period (after 9 months). The 24 h/day wear period will allow to also collect data on sleep quantity.

More information regarding the procedures related to ActivPAL application are stated in the “Procedures” section.

#### Secondary data collection

##### Demographic data

Information on age, sex, country of birth, education, financial status, occupation, and tasks assignment/duties, working hours and years of work, current smoking status, alcohol consumption, presence of chronic disease, usual way of commuting, and structured exercise and SB on week and weekend days will be self-reported trough an online questionnaire. Total use of medication and eventual changes in medications will be collected from the patient records.

##### Body composition and postural inequality assessment

Participants will be weighed to the nearest 0.01 kg while wearing minimal clothes and without shoes, on an electronic scale (TANITA BC-601 scale). Height will be measured to the nearest 0.1 cm with a stadiometer (Seca, Hamburg, Germany). BMI will be calculated as body mass (kg)/height^2^ (m). BMI will be further categorized into normal weight (<25 kg/m^2^), overweight (25–29.9 kg/m^2^), and obesity (>30 kg/m^2^). Waist circumference will be measured with the participants in a standing position, over the naked skin, to the nearest 0.1 cm. The tape is applied horizontally just above the uppermost lateral border of the right ilium at the end of a normal expiration. The mean of two measurements will be considered. If the two measurements differ by more than 1 cm, a third measurement will be performed, and the two closest measurements will be averaged.

Further, body composition will be assessed using bioimpedance (BIA) (101 Anniversary, Akern, Florence, Italy). BIA has been widely used in the sports field for the assessment of body composition and cellular health. BIA is not subject to errors related to prediction equations since it interprets the raw bioimpedance values [resistance (R) and reactance (c)], and it is an easy way to use and non-invasive method. BIA will be performed by a phase-sensitive single-frequency bioimpedance analyzer. Vector length (VL) and phase angle (PhA) will be calculated. This former parameter is an indicator of cellular health. Also, body fat-free mass will be estimated with BIA, while using previous validated equations. Body fat mass will be calculated by subtracting fat-free mass from total body mass. The participants will be fasting for at least 8 h, with a good night sleep, and all metallic accessories will be removed. The participants will be lying down for 5 min prior to this assessment.

Finally, two pictures of the participants will be taken (frontal and lateral), so that postural unbalances can be detected in all assessment moments. This is a simple and quick procedure to assess postural alterations.

##### Psychosocial assessments

**Fatigue and overall discomfort**

The Portuguese version of the Fatigue Scale [63] will be used to evaluate the overall level of fatigue, which comprises 8 items answered on a Likert point scale ranging from 0 (“nothing”) to 4 (“extremely”). Moreover, to specifically address the level of fatigue related to work, the Work Recovery Scale will be used, which has 11 items with dichotomic answer 0 (“no”) and 1 (“yes”). The Work Ability Index of Stanford Presenteeism Scale will be used to assess changes in the ability to work, presenteeism, and job satisfaction; it consists of an 8-item questionnaire answered in a Likert scale ranging from 0 (“no time at all”) to 4 (“the whole time”).

An adapted version of the Nordic Musculoskeletal Questionnaire will be used to assess musculoskeletal discomfort and other health symptoms on the prior week; this questionnaire includes nine regions of the body (neck, shoulders, elbows, hands/wrists, thoracic region, lumbar region, hips/thighs, knees, and ankles/feet) and quantifies pain that participants may feel in each region.

**Life/work satisfaction and quality of life**

To access participants’ perspective about their overall quality of life and satisfaction with life/work, the economic screening measure of the original World Health Organization Quality of Life Instrument-Abbreviated Version (WHOQOL-BREF) will be used. This questionnaire comprises four domains—physical, psychological, environmental, and social—with 2 items each to be answered on a 5-point Likert scale. Response adequate to each statement/item, i.e., the first item has a response from 0 (“very bad”) to 4 (“very good”), with 1 being “bad”, 2 being “not good or bad”, and 3 being “good”. For items 3 and 7, the answers range from 0 (“nothing”) to 4 (“completely”), and the remaining items ranging from 0 (“very unsatisfied”) to 4 (“very satisfied”) [64]. Moreover, participants will be asked to report how they felt in the last 2 weeks, following The World Health Organization-Five Well-being Index (WHO-5), which compresses 5 items, evaluated in a 6-point Likert scale ranging from 0 (“never”) to 5 (“all the time”) [65]. Finally, work-related well-being will be addressed using a shorter version of the original Utrecht Work Engagement Scale (UWES-9), which has 9 items evaluated in a 7-point Likert scale ranging from 0 (“never”) to 6 (“everyday”) [66].

**Eating-related habits/behaviors**

Eating-related habits/behaviors will be assessed using (a) an 11-item original questionnaire assessing the adherence to the Mediterranean diet [67], in which the participants report the weekly consumption of 9 food groups (i.e., (1) non-refined cereals, (2) fruits, (3) vegetables, (4) legumes, (5) potatoes, (6) fish, (7) meat and meat products, (8) poultry, and (9) full-fat dairy products including cheese), plus olive oil use in cooking and alcoholic beverage intake, based on the principles of the traditional Mediterranean Diet, on a scale of 0 to 5 (never, rare, frequent, very frequent, weekly, and daily consumption), and then a composite score is calculated; (b) 5 items assessing specific behaviors such as breakfast consumption, skipping meals, fast food consumption, homemade meals, and take-away meals, answered on a 4-point scale, from never to 6 or more times per week; (c) and 10 items assessing eating behavior traits: Emotional eating will be assessed with an indicator from the Intuitive Eating Scale – 2 (IES-2; “I find myself eating when I’m feeling emotional (e.g., anxious, depressed, sad), even when I’m not physically hungry”) [68]. Eating restriction will be assessed with three indicators adapted from the Dutch Eating Behavior Questionnaire (DEBQ), namely “I often refuse foods or drinks because I am concerned about my weight” (general restraint); “I watch exactly what I eat” (rigid restraint), and “When I have eaten too much, I eat less than usual the following days” (flexible restraint). Two indicators from the IES-2 will be used to measure reliance on hunger and satiety cues (“I trust my body to tell me when to eat”; “I trust my body to tell me how much to eat”), and one indicator from the same scale will measure body-food choice congruence (“I mostly eat foods that make my body perform well”) [69]. External eating will be assessed with two indicators from the Three-Factor Eating Questionnaire (TFEQ-R21), namely “Being with someone who is eating, often makes me want to also eat” and “When I smell appetizing food or see a delicious dish, I find it very difficult not to eat—even if I’ve just finished a meal”. Another indicator from the TFEQ-R21 will also be used to measure uncontrolled/disinhibited eating (“Sometimes when I start eating, I just can’t seem to stop”) [70]. Dimensions with two or more items were calculated by averaging the scores of the corresponding items. Greater values indicate greater levels on that eating trait.
